### Sample size and statistical analysis

#### Power calculation and number of study subjects

This calculation starts with the assumption that the number of exacerbations follows a pure Poisson distribution with a mean rate of 3 per subject per year in the placebo group. A 50% reduction in this rate is considered to be clinically relevant. Hence, in the active treatment group the mean exacerbation rate is set at 1.5 per subject per year. With 33 subjects per treatment group followed up for 1 year, this reduction is detectable with 90% power, given a test size alpha of 0.05 (2-sided).

However, the assumption of a pure Poisson distribution may be too strong. In fact, it is plausible that in this case a zero-inflated Poisson process may be present (the outcome of zero exacerbations has a higher probability than that following from a pure Poisson distribution). In addition there is a risk of overdispersion (the variance is larger than the mean). These phenomena may be expected to have a negative (not exactly quantifiable though) effect on the power of the study.

In order to reasonably compensate for the risk of a too low power and for subjects dropping out within one year follow-up, the number of subjects will be augmented by 40%, so that the sample size is set at 46 subjects per treatment group.

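### The stated 90% power at 33 patients per group does not follow from the stated inputs (about 98%; 90% needs about 22), so the base of the 40% increase is unexplained

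*Protocol article*

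**What the plan says.** The protocol article, under Power calculation and number of study subjects, sets out its premise as follows: "the number of exacerbations follows a pure Poisson distribution with a mean rate of 3 per subject per year in the placebo group". Halving the rate is taken as clinically relevant, so "in the active treatment group the mean exacerbation rate is set at 1.5 per subject per year". The test is two-sided at 0.05. From these inputs the article concludes: "With 33 subjects per treatment group followed up for 1 year, this reduction is detectable with 90% power".

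Only after that figure does the article turn to departures from the Poisson model. It names zero inflation and overdispersion and says: "These phenomena may be expected to have a negative (not exactly quantifiable though) effect on the power of the study". To cover these and dropout it adds 40%, "so that the sample size is set at 46 subjects per treatment group". The abstract's total of 92 agrees with this.

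The Statistical analysis section plans a Poisson regression with a log link and an offset for time on treatment. Standard errors are to be scaled for overdispersion where needed, and a zero-inflated model is to be fitted as well.

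**The concern.** The paragraph gives every input that a Poisson power calculation needs, so its result can be checked directly, and it fails the check. The gap is about 8 percentage points of power, or 11 patients per group on a requirement of 22. Neither rounding nor the choice of a usual test accounts for it.

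The figure is also the base of the final sample size. The 40% is the only stated allowance for overdispersion, zero inflation and dropout together. If the base is not the Poisson requirement, the 40% is not the margin over that requirement, and a reader cannot tell how much protection the 46 per group provides. If some allowance for extra variance is already inside the 33, calling it a pure Poisson figure is wrong and the allowance is counted twice.

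**Working it through.** **Inputs**, all from Power calculation and number of study subjects: rates 3 and 1.5 per patient-year, 1 year, equal groups, variance equal to the mean, two-sided alpha 0.05 (z = 1.960), power 90% (z = 1.2816).

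**1. Attempt to reproduce 33.** For a Wald test of the log rate ratio:

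n per group = (1.960 + 1.2816)² × (1/3 + 1/1.5) / (ln 2)² = 10.507 × 1 / 0.4805 = 21.9, so 22.

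The stated 33 is not reproduced.

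**2. Power at given sizes.** Because 1/3 + 1/1.5 = 1, power = Φ(0.693 × √n − 1.960).

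- n = 22: 90.2%
- n = 33: Φ(2.02) = 97.8%
- n = 46: 99.7%

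**3. Other tests on the same inputs, power at 33 per group.**

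| Method | Power |
|---|---|
| Log rate ratio, pooled null variance | 98.4% |
| Rate difference | 98.2% |
| Square-root transform | 98.5% |
| Exact conditional binomial | 98.1% |
| t-test, simulated | 98.2% |
| Mann-Whitney, simulated | 97.6% |
| Poisson Wald, simulated | 98.3% |
| Poisson with scale correction, simulated | 98.1% |

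Simulations used 10,000 runs each. The exact test reaches 90.3% at 22 per group. Giving both arms the placebo variance of 3, which contradicts a Poisson count with mean 1.5, still yields 94.0% at 33 and needs 29 per group. Reading 33 as the total of both groups gives 80%.

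**4. What would return 33.** Several inputs that the paragraph does not state lead to the same number, because each multiplies the variance term by 1.5 (21.87 × 1.5 = 32.8):

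- a variance/mean ratio of 1.5 in both arms;
- a negative binomial dispersion of 0.25, since 1 + 2 × 0.25 = 1.5;
- a mean exposure of 8 months, since 1 / (8/12) = 1.5;
- rates of 2 and 1, since 1/2 + 1/1 = 1.5.

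These are arithmetically indistinguishable, so the 33 cannot reveal which, if any, was used.

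**5. The increase.** 33 × 1.4 = 46.2, so that step is right, and 2 × 46 = 92. Against the Poisson requirement, 46 / 21.87 = 2.10, a margin of about 110%.

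**6. What that margin tolerates at 3 versus 1.5 with full follow-up.**

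- Variance/mean ratio φ common to both arms: n = 21.87 × φ, so 90% power holds up to φ = 46 / 21.87 ≈ 2.1.
- Variance = mean + k × mean²: n = 21.87 × (1 + 2k), so 90% power holds up to k = (2.10 − 1) / 2 ≈ 0.55. The ratio is then about 2.65 on placebo and 1.83 on active treatment.

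The limit therefore depends on the dispersion model and should not be quoted without it.

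**The case against.** The strongest reply is that nothing in the trial is endangered. The reduction is detectable with at least 90% power at 33, so the sentence understates what the design delivers. The 46 per group, the test, the model and the enrolment target can all stay. The Statistical analysis section already plans a scale correction and a zero-inflated fit, so the validity of the primary test does not rest on a pure Poisson count. All of this stands, and it keeps the point at the level of a non-critical correction. It does not make the printed figure right: a calculated group size for 90% power under listed inputs should be the one those inputs give.

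It might also be said that 33 comes from a cautious calculation. Taking the 29 per group with variance 3 in both arms and dividing by 0.864, a lower-bound efficiency for a rank test, gives 29 / 0.864 = 33.6. But this stacks two approximations that the article does not mention, the planned analysis is not a rank test, and the Mann-Whitney test simulated on the stated rates has 97.6% power at 33.

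Three stronger readings may tempt a reader, and the documents support none of them.

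- *That the planners really meant 2 versus 1 per year.* No section mentions those rates. The article gives 3, derives 1.5 from it by the 50% reduction, and requires three or more exacerbations in the year before entry. The working shows other inputs that fit equally well. Power figures built on 2 versus 1 would rest on a guess.
- *That the article is wrong to call the effect of overdispersion on power not exactly quantifiable.* No dispersion value or excess-zero fraction is given, so the actual effect could not be computed. A tolerance for an assumed value is a sensitivity range, not that effect.
- *That the trial is too large and could be cut.* Applying 40% to 22 gives 30.8, or 31 per group. The article expects extra variance and dropout of unknown size, so nothing in it shows that the surplus is unneeded.

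**Conclusion.** The stated power is wrong as written. With pure Poisson counts, 3 versus 1.5 per patient-year, one year and two-sided 0.05, 33 per group gives about 98% power and 90% needs about 22. This rests only on the article's own inputs and holds across the usual tests. The direction is conservative. The tolerance limits additionally assume full follow-up and the dispersion model named with each. Why 33 was printed cannot be settled from the article. The consequence is limited to the accuracy of the power justification and of the margin it claims.

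**What to change.** Keep 46 per group and correct the paragraph in one of two ways.

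- If 3 versus 1.5 with a pure Poisson count is what was intended: state that 90% power needs 22 per group and that 33 gives about 98%, and describe 46 as about 110% above the Poisson requirement instead of 40%.
- If another input lies behind the 33, such as a variance factor of about 1.5 or different rates: state it with the formula or software used, drop the pure Poisson description if a variance factor was included, and say what the further 40% is meant to cover.

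Optionally, add one sentence on tolerance with its model named: at 3 versus 1.5 and full follow-up, 46 per group keeps 90% power up to a variance/mean ratio of about 2.1 if common to both arms, or up to a negative binomial dispersion of about 0.55.

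The cost is the wording of one paragraph. Patient numbers, the analysis and trial conduct do not change.

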### Statistical analysis

The exacerbation rate (primary efficacy outcome) will be analysed using Poisson regression, with a log link function and the log of the time-under-treatment as offset. The exacerbation rate ratio of active relatively to placebo treatment will be the efficacy parameter of interest that will be tested for significance at the 5% level (2-sided). In addition a 95% confidence interval of this parameter will be calculated. The following baseline covariates will be entered along with treatment group: steroid maintenance therapy, the number of exacerbations in the year preceding randomisation, age, sex, smoking, and the GOLD criteria (Tiffeneau index and FEV1% of predicted). In order to generate hypotheses concerning the modification of the treatment effect by the steroid therapy, the treatment-by-steroid interaction term will be added to the model and its effect will be explored. When necessary, the scale parameter will be used to correct the SEs for overdispersion. Additionally, a zero-inflated Poisson distribution will be fitted to the data in order to test if a better fit is obtained.

Other continuous (secondary) outcome variables with measurements at baseline, 3, 6, 9 and 12 months will be analysed using mixed model ANOVA. The following covariates will be entered in the model along with treatment group: the baseline measurement of the outcome variable, age, sex, smoking and the GOLD criteria. When appropriate, the outcome variables will be suitably transformed in order to obtain normally distributed residuals.

Time to first exacerbation will be analysed using Cox proportional hazards regression with the following covariates entered in the model along with treatment group: age, sex, smoking and the GOLD criteria. Also a Kaplan-Meier curve for time to first exacerbation per treatment group will be presented for illustrative purposes.

Concerning safety, the number and type of adverse event will be compared between the two treatment groups using the chi square (or Fisher’s exact) test.

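### The overdispersion correction to the primary Poisson test is applied only when judged necessary from the outcome data, although the protocol itself doubts pure Poisson; it should always be applied

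*Protocol article*

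**What the plan says.** Under Statistical analysis, the protocol article states that the exacerbation rate "will be analysed using Poisson regression, with a log link function and the log of the time-under-treatment as offset". The target is fixed: "The exacerbation rate ratio of active relatively to placebo treatment will be the efficacy parameter of interest", and it is to be "tested for significance at the 5% level (2-sided)", with a 95% confidence interval and a listed set of baseline covariates.

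Two further sentences deal with departures from the Poisson assumption. The first is "When necessary, the scale parameter will be used to correct the SEs for overdispersion". The second is "Additionally, a zero-inflated Poisson distribution will be fitted to the data in order to test if a better fit is obtained". Neither says what makes the correction necessary or what follows if the zero-inflated model fits better.

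The section on power and number of subjects has already raised both departures. It says that "it is plausible that in this case a zero-inflated Poisson process may be present", and adds: "In addition there is a risk of overdispersion (the variance is larger than the mean)". Of the two together it says: "These phenomena may be expected to have a negative (not exactly quantifiable though) effect on the power of the study". The sample is enlarged by 40% partly for this reason.

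**The concern.** A Poisson model sets the variance equal to the mean. If the counts vary more than that, the uncorrected standard error of the log rate ratio is too small, the test rejects too often, and the 95% interval is too narrow. The protocol foresees this when it sets the sample size, but in the analysis it makes the uncorrected test the default and the correction the exception. The exception is decided from the same outcome data that are being tested. A conditional rule fails in the trials where overdispersion is real but the check does not flag it. How often that happens depends on the trigger.

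The 5% level of the single primary test is at stake. A lesser matter is the status of the zero-inflated fit, since its main coefficient estimates something other than the named efficacy parameter.

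**Working it through.** **Inputs from the protocol article.** Placebo rate 3 per year, one year of follow-up, two-sided 5% level, 33 per group raised by 40%: 33 × 1.4 = 46.2, so 46 per group. The 46 thus follows from the 33. The 33 itself does not follow from the pure Poisson inputs: (1.960 + 1.282)² × (1/3 + 1/1.5) / (ln 0.5)² = 10.51 / 0.480 = 21.9, or 22 per group. That difference is conservative, is a separate matter and does not affect the type I error below.

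**Assumed.** The documents give no dispersion value. I take variance/mean ratios φ from 1 to 3.

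**Link between the two named departures.** Zero inflation by itself produces overdispersion. With extra-zero fraction p and count mean λ, φ = 1 + pλ. Holding the overall mean at 3, λ = 3/(1 − p):
- p = 10%: 1 + 0.1 × 3.33 = 1.33
- p = 20%: 1 + 0.2 × 3.75 = 1.75
- p = 30%: 1 + 0.3 × 4.29 = 2.29

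So calling zero inflation plausible amounts to calling overdispersion plausible.

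**No correction at all.** The true error is about 2Φ(−1.96/√φ): 8.6% at φ = 1.3, 11.0% at 1.5, 16.6% at 2 and 25.8% at 3.

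**Conditional and unconditional correction.** Simulation with 46 per group, both rates 3, negative binomial counts, full follow-up, no covariates, 20,000 runs per row. Two-sided error in %:

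| φ | never | Pearson test p < 0.05 | estimate > 1.5 | estimate > 2 | always |
|---|---|---|---|---|---|
| 1 | 5.0 | 4.9 | 5.0 | 5.0 | 5.0 |
| 1.25 | 8.0 | 6.0 | 7.4 | 8.0 | 4.9 |
| 1.5 | 10.9 | 5.4 | 7.5 | 10.7 | 5.0 |
| 2 | 16.4 | 5.0 | 5.4 | 10.6 | 5.0 |
| 3 | 26.1 | 5.3 | 5.3 | 5.7 | 5.3 |

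With a floor of 1 on the scale, a further 40,000 runs per scenario give 4.4–5.5% for the last column. With truly zero-inflated counts (10–30% extra zeros), always scaling gives 4.6–4.7%, the Pearson trigger at most 5.5%, the 1.5 trigger at most 7.5% and the 2 trigger at most 11.9%.

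**Cost in power.** For pure Poisson counts at 3 versus 1.5 and 46 per group, simulated power is 99.8% with or without the scale. With real overdispersion and the correction always on, normal-approximation power without dropout is 97% at φ = 1.5, 91% at 2, 84% at 2.5 and 77% at 3.

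**Zero-inflated coefficient.** Take a constructed case with zero fractions of 10% (placebo) and 40% (active) and count means of 3.33 and 2.5. The ratio of overall rates is 0.6 × 2.5 / (0.9 × 3.33) = 0.50, while the count-part ratio is 2.5/3.33 = 0.75. The two need not diverge: in simulated negative binomial data with a rate ratio of 0.5, the Poisson and zero-inflated estimates were 0.51 and 0.52 in one setting, and 0.50 and 0.53 in another.

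**The case against.** The strongest reply is that the protocol does provide a correction, and that a numerical trigger is the kind of detail an analysis plan supplies. This article condenses a fuller document and no analysis plan is shown, so the absence of a trigger is not in itself a fault. A sensible trigger also does little harm: the Pearson pre-test stays at or below about 6%. This stands, and it limits the size of the point. It does not remove it, because the stated rule is itself conditional. Writing down a trigger would leave a two-stage procedure where a one-stage procedure holds the level at almost no cost.

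The calculations also omit the planned covariates. Prior-year exacerbations and the others may explain some of the between-patient variation, so residual dispersion may be below the raw ratio. This also stands. The ratios are assumptions, and the lower rows of the table may not apply.

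Four stronger readings are tempting and should not be drawn:
- **That the choice is made on unblinded data.** The article says nothing about blinding at that stage, only what implies use of the outcome data.
- **That the protocol expects overdispersion.** It names it as a risk; what it expects is a loss of power if the departures occur.
- **That the primary test runs at 8–26% error.** Those figures need a correction that is never made, and the plan does provide one.
- **That the efficacy parameter depends on model choice after the data are seen.** The rate ratio is fixed in advance, and scaling does not move the estimate. The zero-inflated model is an additional fit, and nothing says that it replaces the primary model. If it did take over whenever AIC preferred it, simulated error with negative binomial data would be 9.4% at φ = 1.5 and 12.7% at φ = 2 (2,000 runs each), but the text does not describe that procedure.

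**Conclusion.** The point holds in a limited form. The primary test's standard errors are made valid only on condition, in a plan that has itself questioned the assumption behind the uncorrected version. For assumed ratios of 1 to 3, the realised two-sided error lies between about 5% and 11% depending on the trigger (just under 12% in one zero-inflated scenario with the laxest trigger), against about 5% if the scale is always used. These figures rest on 46 per group, equal rates of 3, complete follow-up and no covariates.

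The zero-inflated sentence needs clarification rather than correction: its status should be stated because its count-part coefficient can differ from the named rate ratio. The change is worth making because it is cheap and protects the primary claim. The plan's choice of efficacy parameter is not in question.

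**What to change.** Delete the opening condition. State that the primary Poisson model always estimates the scale as Pearson chi-square divided by its residual degrees of freedom, set to 1 if lower, and that the primary p-value and 95% CI use it.

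Add one sentence: the zero-inflated fit is a sensitivity analysis and does not replace the primary rate ratio; if it is reported, give the implied ratio of overall mean rates alongside the count-part coefficient.

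The cost is two sentences of text. On the log scale the interval widens relative to the uncorrected one by the square root of the estimated scale, for example √1.1 = 1.05 or √1.5 = 1.22, and only when that estimate exceeds 1. Where the conditional rule would have corrected anyway, nothing changes.

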### Secondary study outcome

Measurement of lung function parameters and 6 min walking distance.

Assessment of presence of type D personality by DS14 questionnaire.

Disease specific health related quality of life measured by St. George’s Respiratory Questionnaire (SGRQ).

Generic health status measured by the 12-Item Short Form Health Survey (SF-12).

Indication of anxiety and depression by Hospital Anxiety Depression Scale (HADS).

Microbiology: Sputum specimens will be cultured. Polymerase chain reaction (PCR) in sputum and serology in serum for viral and atypical microorganisms will be performed. The rectal swabs will be tested for change in rectal flora as a result of maintenance azithromycin.

Measurement of inflammatory markers in serum [erythrocyte sedimentation rate (ESR), C-reactive protein (CRP), pro-adrenomedullin, (pro-ADM), interleukin-6 and cytokine profiles of T-helper 1, T-helper 2 and T-helper 17 cells].

Decrease in percentage of clinical versus outpatient department exacerbations.

Difference in treatment effect between subjects with and without steroid maintenance therapy as hypothesis-generating secondary analysis.

Adverse events of treatment. Symptoms that are believed to be (possibly) related to therapy will be reviewed at the outpatient department. If a patient has an adverse event that is thought to be drug related and that does not resolve, then the patient will be withdrawn from the study. There will be no routine ECG screening since azithromycin (in contrast to erythromycin) is much less likely to be a cause of a prolonged QTc interval.

Length of hospital stay.

Time till first exacerbation.

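### The Cox model for time to first exacerbation leaves out prior-year exacerbation count and steroid maintenance, which the primary model of the same events includes: a small, avoidable loss of efficiency in a secondary analysis

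*Protocol article*

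**What the plan says.** The Statistical analysis section of the protocol article gives a separate covariate list for each model.

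- **Primary outcome (Poisson rate model):** treatment plus "steroid maintenance therapy, the number of exacerbations in the year preceding randomisation, age, sex, smoking, and the GOLD criteria", the last being the Tiffeneau index and FEV1 % predicted.
- **Time to first exacerbation (Cox model):** treatment, "with the following covariates entered in the model along with treatment group: age, sex, smoking and the GOLD criteria".
- **Continuous secondary outcomes (mixed models):** treatment, the baseline value of the outcome, age, sex, smoking and the GOLD criteria.

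"Time till first exacerbation" is the last item in the list of secondary outcomes. The Cox list differs from the primary list only by the absence of prior-year count and steroid maintenance, and the article does not explain this.

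**The concern.** Both models analyse exacerbations in the same patients over the same year. Prior-year count is the most direct baseline measure of a patient's tendency to exacerbate. It has to be established for everyone, because three or more events is an inclusion criterion checked against GP and hospital charts. The sample size section itself names overdispersion as a risk. Overdispersion usually reflects patients with different underlying rates, and that is when prior count carries information.

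The plan also adjusts each continuous outcome for its own baseline value. For an exacerbation endpoint, prior-year count is the nearest equivalent. The primary model has it and the Cox model does not.

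At stake are some power on one secondary efficacy endpoint, an estimate somewhat nearer 1, and an unneeded difference in adjustment between two analyses of the same events. The Randomisation section states blocks but no stratification by either factor. A chance imbalance in prior count would therefore be adjusted for in the primary analysis and not in the Cox analysis.

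**Working it through.** **Inputs from the protocol article.** Placebo: "a mean rate of 3 per subject per year in the placebo group". Active: "in the active treatment group the mean exacerbation rate is set at 1.5 per subject per year", so the ratio is 0.5. There are 46 patients per arm, one year of treatment, two-sided alpha 0.05, and entry at three or more prior-year events. The prognostic strength of prior count and of steroid use is not given; it is assumed and varied below.

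**The plan's own figures.** The article states no power for the Cox analysis. For the primary analysis it says "With 33 subjects per treatment group followed up for 1 year, this reduction is detectable with 90% power". The usual pure-Poisson formula gives n = (1.960 + 1.282)² × (1/3 + 1/1.5) / (ln 2)² = 10.51 / 0.480 = 21.9, so 22 per group; 33 per group would give about 98% power. The increase to 46 does reproduce (33 × 1.4 = 46.2). The mismatch at 33 is conservative, separate from this point, and not used below.

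**Cox endpoint without heterogeneity.** The proportions with a first event are 1 − e^(−3) = 0.950 and 1 − e^(−1.5) = 0.777. Expected events are 46 × (0.950 + 0.777) = 79.4. Schoenfeld power is Φ(0.693 × √79.4 / 2 − 1.960) = Φ(1.13) = 87%.

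**Model A: gamma-distributed patient rates.** Take population mean m and dispersion k, and let a = 1/k. A patient with prior count c has expected rate (a + c) / (a/m + 1), so prior count is prognostic. Averaging over patients with c ≥ 3 gives the on-study placebo rate that each choice implies:

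| m, k | Mean prior count given entry | Implied placebo rate per year |
|---|---|---|
| 2, 0.5 | 4.40 | (2 + 4.40)/(1 + 1) = 3.20 |
| 3, 0.5 | 5.18 | (2 + 5.18)/(0.667 + 1) = 4.31 |
| 3, 1 | 6.00 | (1 + 6.00)/(0.333 + 1) = 5.25 |

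Only the first row is close to the protocol's 3 per year. Simulated Cox fits (true hazard ratio 0.5, 46 per arm, no other covariates), without and then with log prior count:

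| Scenario | Hazard ratio | Power | Gain in points |
|---|---|---|---|
| m 2, k 0.5, rate 3.2 (3,000 trials) | 0.543 → 0.528 | 74.1% → 76.6% | 2.5 |
| k 1, rate set to 3.0 (3,000 trials) | 0.551 → 0.534 | 71.4% → 74.7% | 3.3 |
| m 3, k 1, rate left at 5.25 (500 trials) | 0.567 → 0.532 | 72.0% → 81.6% | 9.6 |

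Across the runs with the placebo rate set to 3, the hazard ratio moves from about 0.545–0.56 to 0.52–0.53 and the gain is about 3 to 7 points. The low end comes from reaching a rate of 3 by lowering the population mean. The high end comes from keeping the m 3, k 1 patients and scaling their on-study rates down to 3.

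**Model B: hazard set directly as a power of prior count times a steroid effect.** Placebo mean rate 3, true hazard ratio 0.5, mean prior count about 4.5, 30% on steroids. Both covariates are omitted and then added. Hazard ratios are from a run of 80,000 patients. Power is from 10,000 trials, except 2,000 in the rows marked *.

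| Assumed strength | Hazard ratio | Power | Gain in points |
|---|---|---|---|
| None* | 0.50 → 0.50 | 86.5% → 86.5% | 0 |
| count^0.5, steroid HR 1.25 | 0.51 → 0.50 | 84.3% → 85.3% | 1.0 |
| count^1, steroid HR 1.5 | 0.53 → 0.50 | 77.7% → 84.1% | 6.4 |
| count^1, steroid HR 2 | 0.54 → 0.50 | 75.4% → 83.6% | 8.2 |
| count^1.5, steroid HR 2* | 0.56 → 0.50 | 70% → 83% | about 12 |
| count^1, steroid HR 1.5, residual frailty variance 0.3 | 0.57 → 0.55 | 63.8% → 68.6% | 4.8 |

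Under the null (2,000 trials per scenario), type I error was 4.4% to 6.0% with omission and 4.9% to 6.6% with adjustment.

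**The case against.** The strongest reply is that nothing here is invalid. In a randomised trial the model with fewer covariates targets a less conditional hazard ratio, and its test holds its level. That stands. A reader might infer that the planned estimate is biased by confounding, or that its p-value cannot be trusted; neither follows. Adjustment does not recover 0.50 under Model A either, because one year's count measures a patient's rate imperfectly. Adjusted type I error reached 6.6% in one scenario, so a small part of the simulated gain may come from a slightly liberal Wald test at this sample size.

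The reply also limits the size, rightly. A gain near 10 points appears under Model A only when the placebo rate is allowed to reach 5.25 per year, against the protocol's 3. The larger gains under Model B assume covariate strengths that no document supplies. Both models leave out dropout and the covariates already planned (age, sex, smoking, GOLD criteria); overlap with those would reduce the gain.

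Three further inferences are tempting and unsupported:

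- **That this is the main supportive analysis.** The article gives it no such role, and the trial is not powered on it.
- **That the rate ratio and hazard ratio cannot be compared.** They differ by construction, one using all events and the other the first. Unequal covariates add one avoidable source of difference, worth about 0.02 on the hazard ratio.
- **That the mixed models also need steroid maintenance.** They already adjust for the baseline outcome value, and non-collapsibility does not arise in linear models.

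The evidence for steroid maintenance alone is thin. Model A did not include it, Model B varied it only together with prior count, and the article treats it chiefly as a possible effect modifier.

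The reply does not supply a reason for the difference. The article states a list for each model, so this is a stated choice and not a detail left to a fuller document.

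**Conclusion.** The point holds as a minor one. The Cox model omits two covariates that the primary model of the same events includes, without explanation, and prior-year count is the one that matters. At the protocol's placebo rate, under Model A's assumptions, the cost is an estimate of about 0.55 instead of 0.53 and about 3 to 7 points of power. If prior count is only weakly prognostic the cost is about 1 point, and if it is not prognostic there is none. The analysis as planned is valid and the primary conclusion does not depend on it.

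**What to change.** Before unblinding, give the Cox model the same baseline covariates as the primary model: add the prior-year exacerbation count, preferably on the log scale, and, for consistency, steroid maintenance. If the difference is intended, state the reason. The mixed models need no change on this account.

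The cost is one line of analysis text. Both variables are already needed for the primary model, and the article reports that the trial was still recruiting, so the change can be prespecified. The larger model remains affordable: counting smoking as one term, it has eight coefficients (treatment, age, sex, smoking, two GOLD measures and the two additions) against about 79 expected first events, roughly 10 events per coefficient.
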